### Statistical methods

Analyses will be performed using commercially available software (IBM SPSS Statistics 23, SPSS Inc., Chicago, IL, USA). All data derived from the statistical methods will be given in mean ± standard deviation. Research shows that the most successful athletes in marathon and ultra-marathon running events are frequently those who lose substantially more than 3–4 % BW during competition (Zouhal et al. 2011). Mean body weight of male recreational marathon runners is 73.9 ± 8.1 kg (Barandun et al. 2012) and 75.8 ± 8.6 kg (Friedrich et al. 2014) of male recreational half marathon runners. Mean body weight of female recreational runners is 59.1 ± 6.3 kg (Rüst et al. 2013) and 60.1 ± 7.8 kg (Friedrich et al. 2014) of female recreational half marathon runners. Expected body weight loss during a marathon race is 2.3 ± 2.2 % overall (Zouhal et al. 2011). For male recreational marathon runners we expect a 2.3 % weight loss from 73.9 to 72.2 kg, therefore a sample size of 179 runners is needed to reach 80 % power with two-sided test and alpha of 0.05. For female recreational marathon runners we expect a 2.3 % weight loss from 59.1 to 57.7 kg, therefore a sample size of 159 runners is needed to reach 80 % power with two-sided test and alpha of 0.05. Since body weight loss during a marathon is inversely related to race finishing time (Zouhal et al. 2011) we expect the fastest runners to lose the most relative body weight during competition. Multi-variant regression analyses will be used the determine effects of kind of diet, sex, age, BMI, finished running distances, years of race experience, weekly training load, weekly training frequency, training intensity, in-race food and fluid consumption on individual finishing time (% of overall winners time, ranking, calculated pace). An analysis of variance will be performed to compare individual finishing time (% of overall winners time, ranking, calculated pace), sex, age, body weight, height, BMI, attended running events in past 2 years, finished running distances, personal best time on each distance, number of planned events for 2014/2015, daily/weekly training frequency, daily/weekly training load, period of preparation for main event, aim of race participation, years of running experience, motivation for running then and now, assisted training, years of race experience, training intensity, medium/long-term goal of racing, additional specific kinds of training, specific diet including supplements, specific training/diet prior to race, diet on day of rest/training/race, pre/in/post-race diet, in-race food and fluid consumption, specific gear, relevant medical measures, pre/post-race body weight (including clothing and shoes), calculated weight loss, in-race: nutritional strategy during race, fluid and nutrient intake including breakfast, mood status, and RPE (Borg) whole body/respiratory/legs, among the three subgroups created respective to diet.

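### The ANOVA comparing body weight and height between diet groups states no sex term, although the plan's own figures put men and women about 15 kg apart

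*Protocol article*

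**What the plan says.** All of this is in the Statistical methods section of the protocol article.

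- Body weight is described by sex: "Mean body weight of male recreational marathon runners is 73.9 ± 8.1 kg" and "Mean body weight of female recreational runners is 59.1 ± 6.3 kg". The half-marathon values are 75.8 ± 8.6 kg for men and 60.1 ± 7.8 kg for women.
- The sample size is also by sex. For men: "For male recreational marathon runners we expect a 2.3 % weight loss from 73.9 to 72.2 kg", hence "a sample size of 179 runners is needed to reach 80 % power with two-sided test and alpha of 0.05". For women: "For female recreational marathon runners we expect a 2.3 % weight loss from 59.1 to 57.7 kg", hence 159 runners at the same power and alpha.
- The analysis of variance then covers a long list of variables, among them body weight, height and "pre/post-race body weight (including clothing and shoes), calculated weight loss". The only grouping named is "among the three subgroups created respective to diet". Sex is in this list as one more variable to be compared, not as a factor.
- Sex is an explanatory variable only in the regression, whose outcome is finishing time.

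The Outcomes section places weight, height and weight loss among the secondary outcomes. Body weight before and after the race is recorded in Step 3.

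**The concern.** The plan recognises that men and women must be kept apart when it describes and sizes body weight, but the stated comparison between diet groups does not keep them apart. Two consequences follow.

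**Confounding.** Diet is chosen by the runner. Recruitment runs through several channels, including magazines for vegetarian nutrition and lifestyle, and no balancing by sex is stated. If the share of men differs between diet groups, part of the sex difference in weight and height appears as a diet difference.

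**Precision.** Even with equal shares, the variation between the sexes stays in the error term, so a real diet difference is harder to detect.

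A separate ANOVA of post-race weight also tells the reader little about the race, because most of its variation was already there at the start.

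**Working it through.** **1. The plan's own sample sizes.** A one-sample normal formula with the body-weight SD reproduces both:

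- n = (SD × (1.960 + 0.842) / loss)²
- Men: (8.1 × 2.802 / 1.7)² = 178.2, so 179.
- Women: (6.3 × 2.802 / 1.4)² = 158.9, so 159.

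These numbers size the within-runner weight loss in each sex. They do not size a comparison between diet groups.

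**2. Sex difference in weight.** Marathon: 73.9 − 59.1 = 14.8 kg. Half-marathon: 75.8 − 60.1 = 15.7 kg.

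**3. Bias from unequal sex mix.** The shift between two diet groups is 14.8 kg × the gap in the share of men.

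| Gap (percentage points) | Shift (kg) |
|---|---|
| 0 | 0 |
| 10 | 1.5 |
| 20 | 3.0 |
| 30 | 4.4 |

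The documents do not give the sex mix by diet, so this is a range and not an estimate.

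**4. Share of variance due to sex.** With p the share of men, the between-sex variance is p(1 − p) × 14.8² and the within-sex variance is p × 8.1² + (1 − p) × 6.3².

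| Share of men | Between sexes | Within sexes | Due to sex | SD without / with sex (kg) |
|---|---|---|---|---|
| 179/338 = 53 % | 54.6 | 53.4 | 50.5 % | 10.4 / 7.3 |
| 70 % | 46.0 | 57.8 | 44 % | 10.2 / 7.6 |
| 90 % | 19.7 | 63.0 | 24 % | 9.1 / 7.9 |

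The half-marathon figures give 47.5 % at 179:159 and 23 % at 90 % men.

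**5. Power.** Assumptions: 338 runners (179 + 159) in three equal diet groups, the same sex mix in each, one group heavier by d, alpha 0.05. The noncentrality of the F test is 338 × (1/3) × (2/3) × d² / error variance.

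- d = 3 kg: 676 / 108.0 = 6.26 without sex, power about 60 %; 676 / 53.4 = 12.66 with sex, power about 90 %.
- d = 2 kg: 300.4 / 108.0 = 2.78 without sex, power about 30 %; 300.4 / 53.4 = 5.62 with sex, power about 55 %.

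**6. Calculated weight loss.** "Expected body weight loss during a marathon race is 2.3 ± 2.2 % overall". Applying the same percentage to both sexes, the difference in loss is 2.3 % of 14.8 kg = 0.34 kg. Applying the 2.2 % SD within each sex gives 1.63 kg (men) and 1.30 kg (women). At equal numbers the between-sex variance is 0.25 × 0.34² = 0.029 and the within-sex variance is 0.5 × 1.63² + 0.5 × 1.30² = 2.17. Sex therefore explains about 1 %. Expressed as a percentage of body weight, the expected loss is the same in both sexes.

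**7. Post-race weight.** In men, the SD between runners is 8.1 kg, against about 1.6 kg (2.2 % of 73.9 kg) for the change. A test of unadjusted post-race weight mostly repeats the pre-race comparison.

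The documents give no height figures, so the effect on height is not quantified.

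**The case against.** The best defence is that the ANOVA list is a profile of three self-selected groups. It runs from age and height to gear and motivation. If one diet group weighs less because more of its members are women, the unadjusted difference is a true description. The Limitations section disclaims causality, and the regression for running performance, the main objective, does contain sex. This stands in part: unadjusted means are legitimate as description and should stay. Nor would a significant unadjusted test be a false positive for equal group means, because those means would truly differ. But a reader will take a weight difference in this study as related to diet, and no stated analysis separates the two.

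It can also be said that an analysis of variance need not be one-way, and that covariates for secondary outcomes may sit in a fuller document. However, the article names the method, the outcomes and the grouping, and puts sex among the variables compared. As stated, that is a comparison by diet alone.

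Three stronger readings are tempting and not supported:

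- **That a 15 kg sex difference is read as a diet difference.** This would need one diet group of men only and another of women only. What passes through is 14.8 kg times the gap in the share of men, and nothing if the shares are equal.
- **That the outcome used for sizing is compromised.** Sex explains only about 1 % of the variance in weight loss. The 1.5 to 4.4 kg shifts concern body weight and should not be set against the expected race loss of 1.4 to 1.7 kg.
- **That pre-race weight is ignored.** The planned comparison of calculated weight loss already uses it. Only the separate comparison of post-race weight does not.

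**Conclusion.** The point holds for body weight, height and pre/post-race body weight, all secondary outcomes. The size of the bias is conditional on a sex-mix gap that the documents do not give, so no bias is demonstrated. The loss of precision does not need a gap, but it depends on the overall mix: the figure of about half the variance belongs to near-equal numbers, as in the sized 179:159, and falls to about a quarter at 90 % men. The power figures further assume three equal diet groups and the stated 3 kg or 2 kg difference, neither of which comes from the plan. The change is worth making because it costs almost nothing, but it does not touch the primary outcomes.

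**What to change.** In Statistical methods, state that body weight, height and pre-race body weight are compared between diet groups in a linear model with diet and sex as factors, or are reported separately for men and women as in the sample size. Keep the unadjusted group means as description.

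For the effect of the race, rely on the calculated weight loss already planned, or on post-race weight in a model with diet, sex and pre-race weight. Drop the separate unadjusted ANOVA of post-race weight.

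Cost: one degree of freedom per added term and one sentence of text. Sex and both weights are already collected, so no extra runners or measurements are needed.

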**Fig. 1 Fig1:**
[figure not shown]
Timescale of the NURMI Study

### Step 1

Epidemiological pre-study

Step 1 is composed of a short standardized online questionnaire for endurance and ultra-endurance runners (any distance and any level of performance) primarily in Austria, Germany and Switzerland. Data on sex, age, kind of diet, and running history and habits will be collected. We aim to approach as many runners as possible for this step since gathered data will be used to estimate the prevalence of vegetarians and vegans active in endurance running.

### Step 2

The major NURMI Study questionnaire

Runners matching inclusion criteria of the respective subgroups (capable of running a half-marathon etc./see “Subjects” section) complete an extended questionnaire on health status, specific dietary habits (details of consumption of specific foods or food groups), running history (i.e. preferred running distance, finished races overall and number of completed races in the last 2 years, preparation for a specific event, average distance and training load per day/week, etc.) and exercise induced diet (i.e. during training, racing or a day of rest, nutritional strategy on race day, etc.) as well as quality of life and health-related behavior. Step 2 includes a short form of the Quality of Life questionnaire (QOL BREF 26) distributed by the World Health Organization.

### Step 3

NURMI post-race testing

After individual finishing a race of at least half-marathon distance, runners complete a questionnaire on final ranking, finishing time, energy and fluid intake, in race dietary strategy, and physical and mental perception. The rate of perceived exertion (RPE, overall, leg muscles and respiratory system) will be assessed by using the Borg Scale (Borg 1998).

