#### Inclusion criteria

For the epidemiological pre-study (Step 1) any subject active in running (any distance as well as any performance level) can participate. For successful participation in the main study (Step 2 and 3) a complete data set consisting of the following four items is required: written informed consent (1), at least 18 years of age (2), all NURMI questionnaires completed (3), successful participation in a running event of either half-marathon or marathon distance (4).

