#### Further measurements

Individual finishing time will be measured by the running events professional timing system and will be calculated as percentage of the overall winner’s time.

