#### Secondary outcomes

Outcomes from Step 1 are: nationality, sex, age, body weight, height, calculated BMI, kind of diet, attended races in past 2 years, finished running distances, personal best time on each distance, number of planned events for 2014/2015, in-race food and fluid consumption, daily/weekly training frequency, daily/weekly training load, period of preparation for main event, and aim of race participation.

Outcomes from Step 2 are: years of running experience, motivation for running then and now, assisted training, years of race experience, training intensity, medium/long-term goal of racing, additional specific kinds of training, specific diet including supplements, specific training/diet prior to race, diet on day of rest/training/race, pre/in/post-race diet, specific gear, relevant medical measures, and quality of life and health-related behavior.

Outcomes from Step 3 are: Pre-race: body weight (including clothing and shoes). In-race: individual finishing time, individual runtime as % of overall winners time (calculated), ranking, calculated pace, temperature, wind, air pressure, humidity, sunlight. Post-race: body weight (including clothing and shoes), calculated weight loss, RPE (Borg) whole body/respiratory/legs, mental mood, fluid and nutrient intake including breakfast, and dietary strategy during race.

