### Limitations of the study

Not all vegetarians and vegans participating in running events may be within the reach of the various recruitment methods. Due to various season, daytime and location of races, environment conditions (e.g. weather including sun or rain, temperature, relative humidity) will vary among the respective running events. Furthermore, our study shares with others the limitation of the cross-sectional design; therefore the present investigation allows no conclusion regarding causality. Prospective cohort studies are needed to confirm the associations between specific kinds of diet, health status and endurance performance to assess the causal direction and to develop recommendations for nutritional intake for vegetarian and vegan runners for training and racing.

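### The diet-group ANOVA for in-race intake, weight loss, exertion and mood takes no account of race distance, so a difference in distance mix cannot be told from a difference in diet

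*Protocol article*

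**What the plan says.** **The comparison.** Statistical methods in the protocol article gives one ANOVA for a long list of variables. It opens "An analysis of variance will be performed to compare individual finishing time (% of overall winners time, ranking, calculated pace), sex, age, body weight, height, BMI" and ends "fluid and nutrient intake including breakfast, mood status, and RPE (Borg) whole body/respiratory/legs, among the three subgroups created respective to diet". In-race food and fluid consumption and calculated weight loss are on the same list. No covariate, stratum or second factor is given.

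**The adjusted model.** The multivariable regression in the same section does not cover these outcomes. Its outcome is finishing time, and intake enters only as a predictor: "training intensity, in-race food and fluid consumption on individual finishing time (% of overall winners time, ranking, calculated pace". Weight loss, perceived exertion and mood do not appear in it.

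**The races.** Inclusion criteria requires "successful participation in a running event of either half-marathon or marathon distance (4". The description of Step 3 sets no upper limit: "After individual finishing a race of at least half-marathon distance, runners complete a questionnaire on final ranking, finishing time, energy and fluid intake".

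**The units.** Finishing time has a scaling to the race, since under Further measurements it "will be calculated as percentage of the overall winner’s time". Secondary outcomes lists the post-race variables as "calculated weight loss, RPE (Borg) whole body/respiratory/legs, mental mood, fluid and nutrient intake including breakfast, and dietary strategy during race". It gives no rate for intake and no unit for weight loss.

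**The acknowledged differences between races.** Limitations of the study says that "environment conditions (e.g. weather including sun or rain, temperature, relative humidity) will vary among the respective running events", and attributes this to season, time of day and location. Distance is not mentioned.

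**The concern.** Total food and fluid taken during a race depends on how long the race lasts. Weight loss, exertion and mood at the finish may also differ between a half-marathon and a marathon. The design is cross-sectional and the races are self-selected, so nothing makes the distance mix equal across omnivores, vegetarians and vegans. If one group contains more marathon runners, the stated ANOVA can report a difference between diets in race nutrition when runners of every diet eat and drink at the same rate.

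Strengths of the study names in-race dietary consumption among the comparisons to be delivered, and the Background expects the results to help shape nutrition strategies for vegetarian and vegan runners. A difference produced by distance would mislead that use. The point concerns the secondary race-response outcomes, not the finishing-time measures.

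**Working it through.** **Stated figures.** The article gives no figure for this comparison. Its only sample sizes are for the change in body weight over a marathon, and both reproduce from n = ((1.960 + 0.842) × SD / difference)²:
- Men: SD 8.1 kg, difference 73.9 − 72.2 = 1.7 kg, n = 178.2, so 179.
- Women: SD 6.3 kg, difference 59.1 − 57.7 = 1.4 kg, n = 158.9, so 159.

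They size a before-after change within each sex, not a comparison of diets, so they do not bear on this point.

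**Inputs for the illustration.** From Statistical methods: marathon weight loss 2.3 % with SD 2.2 %. Assumed, because the documents do not give them: fluid 400 mL/h (SD 160) in every diet group, half-marathon 2.0 h, marathon 4.25 h, weight loss over a half-marathon of 1.15 % (half the marathon figure), and groups of 150, 60 and 90. There is no diet effect. Only the marathon share p varies by group.

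**Total fluid, shares 50/40/30 %.**
1. Group mean = 400 × (2.0 + 2.25p), which gives 1250, 1160 and 1070 mL.
2. Group variance = 160² × (4.25²p + 2.0²(1 − p)) + 400² × 2.25² × p(1 − p), which gives 484,900, 440,800 and 380,500. Weighted by group size, this is 444,760.
3. The overall mean is 1178 mL. The between-group sum of squares is 150 × 72² + 60 × 18² + 90 × 108² = 1,846,800.
4. Noncentrality = 1,846,800 / 444,760 = 4.15. With 2 and 297 degrees of freedom at the 5 % level, the rejection probability is about 43 %.

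**Percentage weight loss, same shares.** Means are 1.15 × (1 + p) = 1.725, 1.61 and 1.495 %. The pooled variance is 5.15, the noncentrality 0.585, and the rejection probability about 10 %.

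**All mixes.** Simulation (4,000 trials per scenario in the runs that record a count) and the closed form above agree closely. The ranges cover both.

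| Marathon shares | Total fluid, diet-only ANOVA | Weight loss (%), diet-only ANOVA |
|---|---|---|
| equal | 5 % | 5 % |
| 50/45/40 % | 12–13 % | 6–7 % |
| 50/40/30 % | 40–43 % | 9–10 % |
| 50/35/20 % | 79–83 % | 15–16 % |

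With a distance term, both outcomes return to about 5 %.

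**Other assumptions.** A separate simulation used 338 runners in near-equal groups, 2 h and 4 h, and 0.5 ± 0.2 L/h. For total fluid it gave 5 % at 40/40/40, 13 % at 40/35/30, 24 % at 45/35/30 and 56 % at 50/35/25. Weight loss gave 5, 7, 7 and 13 %. With a distance term the rate was about 5 % throughout.

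**Is intake per hour enough?** Only if the hourly rate is the same at both distances. Assume 300 mL/h in the half-marathon and 450 mL/h in the marathon, still with no diet effect. At 50/40/30 the mean rates are 300 + 150p = 375, 360 and 345 mL/h, the pooled variance is 30,910, the noncentrality 51,300 / 30,910 = 1.66, and the rejection probability about 19 %. The three unequal mixes give about 8, 19 and 40 %. A distance term restores about 5 %.

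**Exertion and mood.** The documents give no values by distance, so no calculation is possible.

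**The case against.** **Silence is not a statement.** The section is a condensed paragraph, and units and covariates for secondary outcomes are often left to a fuller document. A reader might infer that raw totals will be analysed with both distances pooled. The text says neither. What stands is narrower: the article names the method, the outcomes and the grouping, gives finishing time both a scaling and an adjusted model, and gives these outcomes neither.

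**Distance may be covered elsewhere.** Primary outcomes words the performance outcome as marathon time, but nothing limits Step 3 intake, exertion or mood to marathons. Finished running distances appears in the ANOVA list, but Secondary outcomes places it in Step 1 beside personal bests. It reads as running history, and in the ANOVA it is a variable being compared, not an adjustment.

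**Weight loss may already be a percentage.** Statistical methods discusses it largely in relative terms, so this is plausible. It would not remove the distance question, and the weight-loss figures above already use percentages.

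**Time on the course.** A reader might infer that longer time on the course by itself inflates weight loss, even within one distance. The documents contradict this: Statistical methods says that weight loss in a marathon is inversely related to finishing time. Only the contrast between distances remains, and its size rests on the assumed half-marathon loss.

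**No imbalance is shown.** A reader might infer that false diet differences will occur. No section says that distance mix differs by diet, and with equal mixes the error rate stays at 5 %. The design does not exclude imbalance either. The disclaimer on causality in Limitations of the study is sound but would not alert a reader to this particular source of difference.

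**Conclusion.** The point holds in conditional form. As written, the ANOVA cannot separate a diet difference in the Step 3 race-response outcomes from a difference in race distance, should the distance mix differ by diet. Under the assumed rates, durations, group sizes and unequal marathon shares, the effect is large for total intake (about 12 to 80 % false positives) and small for percentage weight loss (about 6 to 16 %). It cannot be quantified for exertion and mood, and it is absent when the mixes are equal. These outcomes are secondary, but the correction is cheap, uses data already collected, and should be made before analysis.

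**What to change.** In Statistical methods, replace the diet-only ANOVA for the Step 3 race-response outcomes:
- Include race distance (half-marathon or marathon) as a factor beside diet, or analyse within distance, for all of them: in-race food and fluid intake, weight loss, perceived exertion and mood.
- Express in-race intake per hour of finishing time and keep breakfast separate. The per-hour unit does not replace the distance factor.
- Define calculated weight loss as a percentage of pre-race weight.
- Report the number of runners by diet and distance, so that readers can see whether the mix differs.

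The cost is one degree of freedom with two distances and slightly more analysis work. If longer races are kept, as the Step 3 wording allows, the factor needs further levels. Analysing within distance leaves fewer runners per comparison, which favours the factor where a diet group is small. No new data collection is needed.
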